**Statistical analysis.**

The crude probability of recovery at 14^th^ day will be compared by Chi-Square test. A covariate‐adjusted estimation of the ratio of probability of recovery in experimental treatment to standard of care will be based on the standardization approach of Ge et al. (2011; Ge, M., Durham, L.K., Meyer, R.D., Xie, W. and Thomas, N. (2011) Covariate‐adjusted difference in proportions from clinical trials using logistic regression and weighted risk differences. Drug Information Journal, 45, 481–493). Covariates to be included will be age, sex, basal punctuation in WHO scale at baseline and presence of cardiovascular risk factors.

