## Other complications that are unforeseeable may also occur. The most serious complications usually occur within the first month after T cell or NK cell infusion.

1. STUDY POPULATION

The target population for enrolment in the study will be patients with pneumonia or lymphopenia related to COVID-19.

- Pneumonia will be diagnosed as an acute respiratory disorder characterized by the presence of cough and at least one of the following: new-onset focal chest signs, fever for more than 4 days or dyspnea/tachypnea.
- Lymphopenia will be defined as lymphocyte counts below 1.2×10⁹.

A total of 182 patients will be included in this clinical trial. The plan is to enroll 18 patients in the first dose escalation segment (phase I): 9 patients per arm (3 patients in each cohort for both arms).

A total of 164 patients will be included in the phase II: 82 patients per arm.

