**Sample Size**

Sample size has been calculated under the hypothesis of superiority of intervention versus standard of care assuming a one tailed alfa error of 0.05 and beta error of 0.2. According to the study with Remdesivir by Beigel et al (PMID: 32445440; DOI: 10.1056/NEJMoa2007764), a 42% of patients with basal punctuation of 4 to 6 at day 15 in the WHO ordinal scale recovered. A similar estimation (40%) is made by Rai et al (Rai, S.N., Qian, C., Pan, J. et al. Statistical design of Phase II/III clinical trials for testing therapeutic interventions in COVID-19 patients. BMC Med Res Methodol 20, 220 (2020). https://doi.org/10.1186/s12874-020-01101-z) for patients on intermediate risk (3 to 5 in this same scale). Based on these assumptions the table below shows the sample size for relative risks of 0.7 and 0.65 and recovery percentage of 40%, 45% and 50% in the standard of care group. Therefore, the objective is to recruit 82 patients per arm.

| **RR** | **P1** | **P2** | **SEnvelop** |
| --- | --- | --- | --- |
| 0.7 | 40 | 57.14 | 104 |
| 0.7 | 45 | 64.29 | 82 |
| 0.7 | 50 | 71.43 | 64 |
| 0.65 | 40 | 61.54 | 64 |
| 0.65 | 45 | 69.23 | 50 |
| 0.65 | 50 | 76.92 | 37 |

P1: percentage of recovery in standard of care group;

P2: percentage of recovery in intervention group.

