**Phase II**

The primary outcome in Phase II in this study is:

- The incidence of patient recovery infusing adoptive NK cells or adoptive memory T cells.
- **Recovery is defined as:** Proportion of participants in each group with normalization of fever and oxygen saturation [criteria for normalization: temperature < 38°C armpit, and SpO2 > 94%, sustained for at least 24 hours] or lymphopenia recovery **through Day 14.**

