# General considerations

Tabular summaries will be presented by treatment group.

Categorical data will be summarized by number and percentages. Continuous variables will be summarized by descriptive statistics. Recover incidence (RI): Time to recovery.

The overall survival rate will be calculated by the nonparametric Kaplan-Meier method. Fisher exact test will be used to identify those patient characteristics that are significantly associated with treatment response (complete or partial).

For quantitative characteristics a chi-squared trend test will be conducted to examine whether the proportion of patients responding to treatment either increased or decreased across the levels of the characteristic.

The results of the statistical analysis will be displayed in the tables and as mean ± SD in the Figures. Levels of significance will be expressed as p-values (*p < 0.05).

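### The only stated test of day-14 recovery is a crude chi-square, while the planned covariate-adjusted ratio has no deciding role: a loss of efficiency and coherence, not an error

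*Protocol*

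**What the plan says.** The phase II primary outcome is binary: "The incidence of patient recovery infusing adoptive NK cells or adoptive memory T cells", with recovery assessed through Day 14 (Study outcome measures, Primary outcome).

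The Statistical analysis paragraph in the Study population section names two analyses of it:

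- The crude probability of recovery at the fourteenth "day will be compared by Chi-Square test".
- Alongside that test, the paragraph plans an analysis adjusted for baseline covariates, described as an "estimation of the ratio of probability of recovery in experimental treatment to standard of care will be based on the standardization approach" from a cited methods paper. Its covariate list reads: "Covariates to be included will be age, sex, basal punctuation in WHO scale at baseline and presence of cardiovascular risk factors".

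The first is the only between-group test of recovery that the protocol names. The second is an estimate: no test is attached, it is not called primary or supportive, and nothing says which result prevails if the two differ. The General considerations section of the statistical chapter adds a 0.05 threshold without sidedness and no adjusted test.

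The Sample Size paragraph works from two unadjusted proportions with a "one tailed alfa error of 0.05 and beta error of 0.2". The row that sets the target is "0.7 | 45 | 64.29 | 82".

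**The concern.** Phase II admits patients ranging from no supplemental oxygen to non-invasive ventilation, and the protocol selects the baseline ordinal score as a covariate. It states 1:1 randomisation within each HLA-defined arm and names no stratification by severity, so chance imbalance in severity is left to the analysis.

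If the covariates predict recovery, a test that ignores them is less powerful than one that uses them, and the adjusting model will be fitted anyway. The p-value would also come from one analysis and the adjusted effect from another. A report could then show a non-significant chi-square beside an adjusted ratio whose interval excludes 1, or the reverse, with no stated rule for choosing between them.

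**Working it through.** **1. Reproduce the plan's figure.** Inputs from the Sample Size table: P1 = 0.45, ratio 0.7, so P2 = 0.45/0.7 = 0.6429; one-sided 5%, power 80%. Pooled-variance formula, no continuity correction:

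n = [1.645 × √(2 × 0.5464 × 0.4536) + 0.842 × √(0.45 × 0.55 + 0.6429 × 0.3571)]² / (0.6429 − 0.45)²

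= (1.158 + 0.581)² / 0.1929² = 3.025 / 0.0372 = 81.3, rounded up to 82 per randomised group.

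This is the stated 82, for an unadjusted comparison. Power of the crude test at 82 per group is 80.3%. The sizing and the chi-square therefore match, if the test is read one-sided.

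**2. Group sizes.** The protocol states: "A total of 164 patients will be included in the phase II: 82 patients per arm". Each HLA-defined arm is then randomised 1:1 (Subject Treatment Assignment), and 82/2 = 41 per group. Crude power there is 54.4%. Both sizes are shown below.

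**3. Compare the two tests by simulation.** Recovery is 45% v 64.29%, one-sided 5%, 6000 trials per setting. Four independent covariates form a prognostic score with standard deviation s on the log-odds scale. The documents give no value for s, so it is an assumption. One standard deviation of the score multiplies the odds of recovery by e^s, which is 1.6, 2.7 and 4.5 for s = 0.5, 1.0 and 1.5.

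- Crude: z = (p̂₁ − p̂₀) / √(2p̄(1 − p̄)/n), the one-sided form of the uncorrected chi-square.
- Adjusted: fit a logistic model with treatment and covariates; average the predicted probabilities over all patients with treatment set to 1 (m₁) and to 0 (m₀); z = log(m₁/m₀)/SE, with a delta-method SE.

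| Per group | s | Crude power | Adjusted power | Change (points) | Different significance conclusions |
|---|---|---|---|---|---|
| 82 | 0 | 80.1% | 79.1% | −1.0 | 3.3% |
| 82 | 0.5 | 80.2% | 81.5% | +1.3 | 6.1% |
| 82 | 1.0 | 80.2% | 86.1% | +5.9 | 10.5% |
| 82 | 1.5 | 80.4% | 90.5% | +10.1 | 13.4% |
| 41 | 0 | 54.1% | 53.2% | −0.9 | 7.0% |
| 41 | 0.5 | 53.3% | 54.7% | +1.4 | 10.2% |
| 41 | 1.0 | 54.6% | 60.9% | +6.3 | 16.2% |
| 41 | 1.5 | 55.0% | 67.7% | +12.7 | 22.0% |

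The Monte Carlo standard error of each power is at most about 0.65 points.

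**4. Effect of the standard error.** I repeated the runs with an influence-function (robust) standard error, 4000 trials per setting. The degrees-of-freedom correction multiplies the variance by N/(N − 6), where N is the total in the comparison and 6 the number of model coefficients. At 41 per group with s = 0, corrected adjusted power is 53.3% against 55.0% crude, a change of −1.7. Disagreement in that setting is 6.2% without the correction and 6.6% with it. This sets the lower ends of about −2 points and 6% at 41 per group.

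**5. Type I error.** With the delta-method SE the adjusted test rejects in 5.0-5.7% of null trials over both sizes. With the uncorrected robust SE at 41 per group it is 5.2-6.1%; with the correction it is 4.6-5.3%.

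**6. A different covariate model.** With three severity levels, age, sex and cardiovascular risk, let each severity step multiply the odds of recovery by 0.41, 0.26 or 0.17. Adjusted power is then 84%, 87% or 92% against about 81% crude at 82 per group, and 57%, 61% or 67% against 54-55% at 41. At 0.58 per step there is no material gain.

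**The case against.** The strongest case on the other side is that nothing here is wrong. A chi-square on a randomised binary endpoint is valid, and it is the test for which the trial was sized. The protocol never labels it primary. Which analysis decides, and with which variance estimator, is often left to a statistical analysis plan, and that document is not at hand. The validity argument stands in full. The deferral argument stands in part: the protocol itself fixed the test, the adjusted method and the covariates, and attached the test to the less efficient of the two.

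The gain is also an assumption. Recovery can be met through lymphopenia recovery alone, and the saturation criterion is not stated to be on room air. Both features could weaken the link with baseline oxygen support. This stands, and it is why only a range is given.

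A reader might infer more than the documents support:

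- **That the chi-square leaves the trial underpowered.** It does not. Power at 82 per group is 80% as planned; the 54% at 41 per group comes from how 82 is split, and even the strongest scenario reaches only about 68% there.
- **That the two analyses can point in opposite directions or answer different questions.** Both target the same marginal effect. What was computed is disagreement about crossing the significance threshold.
- **That the adjusted test has exactly the same error rate.** At 41 per group it is slightly loose without a small-sample correction.
- **That the covariates are ready to use.** The covariate is called the WHO scale, but the schedules collect NEWS and a 7-point scale. The Sample Size paragraph cites baseline scores of 4 to 6, whereas on Appendix 2 categories 5 and 6 mean mechanical ventilation or ECMO, which phase II excludes. The two scales are therefore not shown to be the same. Cardiovascular risk factors are not defined.

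**Conclusion.** The point holds as a worthwhile but optional improvement. The protocol gives its only test of recovery to the crude comparison and leaves the better-informed analysis without a role or a rule of precedence.

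The effect on power runs from about −1 to +10 points at 82 per group and about −2 to +13 at 41. Significance conclusions differ in about 3-13% and 6-22% of trials respectively. These figures assume the plan's 45% v 64.29%, a one-sided 5% test, a correctly specified logistic model, and a prognostic strength that the documents do not supply. With weak covariates there is no gain. The chi-square being the only named test does not make the trial invalid or lower its power below plan.

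**What to change.** Before data are seen, state that:

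- the standardised marginal ratio of recovery probabilities, with its confidence interval and a robust standard error carrying a degrees-of-freedom correction, is the primary test and the primary estimate;
- the crude chi-square is supportive, and is the pre-specified fallback if the model does not converge;
- the baseline severity covariate is the 7-point scale of Appendix 2 as recorded at screening/Day 0;
- cardiovascular risk factors are derived from the medical history by a listed definition.

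No new data collection is needed. The cost is that the model form and the covariate definitions must be fixed in advance, and that about 1 to 2 points of power are lost if the covariates turn out to be useless. The change does not repair the 41-per-group shortfall, which needs its own correction.

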******Figure 1. Schematic representation of procedure for blood donor obtention**

## Inclusion criteria

Patients eligible for inclusion in this study have to meet all of the following criteria:

- Male or female patients ≤ 80 years of age.
- Patient with diagnosis of COVID-19 infection with laboratory confirmation by reverse-transcription PCR (RT-PCR) of SARS-CoV-2 or other methods used according to each center protocol prior to study entry.
- Onset of symptoms < 12 days prior to administration of study treatment.
- **Phase I criteria:** Patients requiring hospitalization for COVID-19, with **pneumonia** diagnosed with chest radiograph or computed tomography imaging or **lymphopenia** (absolute lymphocyte counts below 1.2 x 10^9^cells /L) **AND** O_2_Sat ≤ 94% on room air at screening, no oxygen requirement or with an oxygen need of **≤ 2.5 lpm** in nasal cannula.
- **Phase II criteria:** Patients requiring hospitalization with **pneumonia** diagnosed with chest radiograph or computed tomography imaging or **lymphopenia** (absolute lymphocyte counts below 1.2 x 10^9^cells /L) **AND** O_2_Sat ≤ 94% on room air at screening, requiring or not oxygen supplementation (nasal cannula, oxygen mask with reservoir, non-invasive ventilation, etc), but **excluding** mechanical ventilation.
- Have a negative pregnancy test documented prior to enrollment (for females of childbearing potential).
- Be willing and able to comply with study procedures.
- Patients with the ability to comprehend and sign the informed consent
- Written informed consent obtained prior to any screening procedures.

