## Subject Treatment Assignment

Patients will be allocated into two groups: Arm A and Arm B depending on HLA typing.

For the phase I, patients on each arm will subsequently undergo a correlative allocation into the different cohorts (1,2,3).

The decision to proceed to each subsequent dose level (next cohort) will be made based on safety and tolerability data from the prior lower dose level. Safety data for at least 7 days post-dose from all the subjects at the prior lower dose will be reviewed before dose escalation.

The next cohort will open if all the patients in the previous cohort have been included and no safety issues have aroused during the follow-up after cell infusion (data of at least 7 days after cell infusion is required to proceed to each subsequent dose). Patients will continue to be followed for possible DLTs during the 21 days following cell infusion.

For phase II, eligible patients will be allocated to arm A or B considering HLA typing and within each arm they will then be randomized in a 1:1 ratio to 1 of 2 treatment groups (SoC or SoC+RP2D).

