**If the screening and Day 0 visits occur within 24 hours, no procedures need to be repeated.**

Participants must complete the following assessments before administering the study drug (if not done in the previous 24 hours):

- Physical examination including, vital signs (heart rate, temperature, blood pressure, and body weight).
- Documentation of respiratory status:
- Respiratory Rate
- SpO2 at rest or PaO2
- FIO2
- Oxygen supplementation:
  - nasal cannula
  - high flow oxygen therapy
  - mask with a reservoir bag
  - non-invasive ventilation
- Radiographic findings if available.
- Obtain blood samples for:
- Hematology and coagulation: Hematocrit, Hemoglobin, Mean Corpuscular Hemoglobin Concentration (MCHC), MCV (Mean Corpuscular Volume), Platelets, Red blood cells, White blood cells with differential (Basophils, Eosinophils, Lymphocytes, Monocytes, Neutrophils). **D-Dimer.**

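### The covariates fixed for the adjusted phase II recovery ratio leave out baseline lymphopenia status, which is built into the primary outcome and already collected

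*Protocol*

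**What the plan says.** The Statistical analysis paragraph (Protocol, Study Population) has two parts. Crude recovery at day 14 is compared by chi-square test. Separately, a ratio of recovery probabilities is estimated by standardisation from a logistic model, with a closed list: "Covariates to be included will be age, sex, basal punctuation in WHO scale at baseline and presence of cardiovascular risk factors".

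Under Study Outcome Measures, Phase II, recovery can be reached in two ways by Day 14: "normalization of fever and oxygen saturation" held for at least 24 hours, or recovery of lymphopenia.

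The Inclusion criteria admit phase II patients with pneumonia or lymphopenia, the latter defined as "absolute lymphocyte counts below 1.2 x 10"^9 cells/L, so lymphopenia is not required of everyone. Room-air saturation of 94% or below is required of everyone.

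The lymphocyte count is collected at screening and again before infusion. The Baseline/Day 0 blood samples include "White blood cells with differential (Basophils, Eosinophils, Lymphocytes, Monocytes, Neutrophils". Temperature and a measure of oxygenation are also recorded.

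The sample size is set "assuming a one tailed alfa error of 0.05 and beta error of 0.2", and within each HLA-defined arm "within each arm they will then be randomized in a 1:1 ratio to 1 of 2 treatment groups (SoC or SoC+RP2D").

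**The concern.** One of the two routes to the primary outcome depends on whether the patient was lymphopenic at entry, and no listed covariate records that. Age, sex and cardiovascular risk factors do not. A baseline severity score built on level of care and oxygen support, like the 7-point scale in Appendix 2, does not either.

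The tie is structural and needs no outside evidence. If lymphopenia recovery requires lymphopenia beforehand, only patients who are lymphopenic at entry have the second route. If a normal count is enough, patients without lymphopenia satisfy that route from the start. On either reading baseline status bears on the outcome.

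At stake is the quality of the adjusted ratio. A chance difference between the groups in the share of lymphopenic patients would go uncorrected, and any variance that lymphopenia explains would stay in the interval. The list is stated in the protocol itself, so this is not a detail left open for a later plan.

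**Working it through.** **Inputs from the protocol.** One-sided alpha 0.05 and power 80%; recovery 45% with standard of care and 45/0.7 = 64.29% with intervention (table row "0.7 | 45 | 64.29 | 82"); "Therefore, the objective is to recruit 82 patients per arm"; 1:1 allocation within each arm.

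**Input not in the protocol.** The prognostic strength of baseline lymphopenia. It is an assumption throughout and is shown as a range.

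**1. The plan's own figure.** Two proportions, pooled variance under the null, no continuity correction:

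n = [1.645 x sqrt(2 x 0.5464 x 0.4536) + 0.842 x sqrt(0.45 x 0.55 + 0.6429 x 0.3571)]^2 / 0.1929^2 = 81.3, so 82 per compared group (power 80.3%).

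This matches the stated 82. No covariate enters the calculation.

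**2. Size of the compared groups.** The formula gives 82 per compared group, whereas 82 patients per HLA arm split 1:1 leave about 41 per group. That is a separate issue, so both sizes are shown.

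**3. What an added covariate could gain.** Suppose the adjusted estimate were tested at one-sided 0.05 and the new term removed a share R2 of the variance. As a normal approximation on the difference scale:

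Power = Phi( delta / (SE x sqrt(1 - R2)) - 1.645 ), with delta = 0.1929 and SE = sqrt(0.4771 / n).

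SE is 0.1079 at n = 41 and 0.0763 at n = 82.

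| Assumed R2 | 41 v 41 | 82 v 82 |
| --- | --- | --- |
| 0 | 55.7% | 81.2% |
| 1% | 56.0% | 81.5% |
| 10% | 59.5% | 84.6% |
| 15% | 61.6% | 86.4% |

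The gain at 10 to 15% is about 4 to 6 points at 41 v 41 and 3 to 5 at 82 v 82. At 1% it is under half a point. The starting row uses the unpooled variance, hence 81.2% rather than 80.3%.

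**4. Is 10 to 15% plausible?** Suppose half the standard-of-care patients are lymphopenic and overall recovery is 45%.
- Recovery of 65% in lymphopenic and 25% in other patients gives R2 = 0.25 x 0.40^2 / (0.45 x 0.55) = 16%.
- Recovery of 50% and 40% gives R2 = 0.25 x 0.10^2 / (0.45 x 0.55) = 1%.

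Both splits are invented. The protocol does not favour either.

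**5. Chance imbalance.** With half the patients lymphopenic and 41 per group, the SD of the between-group difference in lymphopenia is sqrt(2 x 0.25 / 41) = 11 percentage points. Under the 65% v 25% split, one SD moves the recovery difference by 0.11 x 40 = 4.4 points, against a planned 19.3. Under 50% v 40% it moves it by 1.1 points.

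**6. Room for extra terms.** Expected non-recoveries at 41 v 41 are 41 x 0.55 + 41 x 0.3571 = 37. Counting treatment and one term per covariate, and leaving out the intercept, the listed model has 5 parameters (7.4 events each). Adding lymphopenia makes 6 (6.2 each). Adding lymphopenia, saturation and temperature makes 8 (4.6 each).

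**The case against.** The strongest reply is that nothing here is an error. The comparison is a crude chi-square test, and the covariates serve only a separate estimate. Under randomisation, leaving out a prognostic covariate biases neither one. The four listed covariates are sensible and fixed in advance, and preferring others is a matter of optimisation. All of this stands.

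A reader might infer that the trial loses power below its 80%. The documents do not support that. The 82 comes from an unadjusted calculation, and no covariate list can change the power of the crude test. The power figures above describe a test of the adjusted estimate that the protocol does not specify.

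The size is also open. The Background section on cell therapy says lymphocyte counts are lower in severe cases, who may reach the fever and saturation route less often. That would work against the extra route open to lymphopenic patients, and the net association could be small.

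A reader might also infer that saturation and temperature must be added as equally direct predictors. The case for them is weaker. Everyone enters with room-air saturation at or below 94%, so its range is restricted, and a severity score can be expected to carry part of the oxygen need. PaO2 may be recorded in place of SpO2, so an SpO2/FiO2 ratio need not exist for every patient. The event count at 41 v 41 leaves little room.

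What remains is baseline lymphopenia: tied to the outcome by its definition, already collected, and absent from a closed list.

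**Conclusion.** The point holds as a modest improvement to a pre-specified list. The adjusted recovery ratio omits a baseline variable that is part of the outcome's own definition. The result is neither bias nor a shortfall in planned power, but possible precision and correction of chance imbalance not taken.

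The benefit starts at about none. It reaches about 4 to 6 points of power at 41 v 41, or 3 to 5 at 82 v 82, only if lymphopenia removes 10 to 15% of the variance beyond the listed covariates and the adjusted estimate is tested. Both conditions are assumptions. The adjustment repairs neither the group-size question nor the unclear meaning of lymphopenia recovery in a patient who was never lymphopenic. Those need their own corrections.

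**What to change.** In the Statistical analysis paragraph, add one baseline lymphocyte term to the listed covariates: either lymphopenia yes/no at the protocol's threshold of 1.2 x 10^9/L, or the absolute lymphocyte count. Choose the form in advance and define it as the last value before randomisation. That wording matters because Day 0 samples are required only before infusion, and screening values may stand in for them.

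Settle the meaning of lymphopenia recovery at the same time. If a normal count alone were enough, every patient without lymphopenia would count as recovered, and a yes/no term would predict the outcome perfectly in that stratum, which a logistic model handles badly.

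Room-air saturation from screening and baseline temperature may be added if the number of events allows.

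The cost is one clause and one model parameter, with no new visits, samples or patients. Make the change before outcome data are seen, since a term added later would look data-driven.

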Recent and previous data from our group and others have shown that infusions of donor memory T-lymphocytes, CD45RA- T cells, are safe and constitute a simple measure to prevent infections in the setting of allogeneic hematopoietic stem cell transplantation (HSCT). This immunological memory will create a more rapid and robust secondary immune response to COVID-19.

In summary, to maintain an efficient antiviral immune response, we need two mechanisms: first, we need both a rapid and well-coordinated innate immune response since it is the first line of defense against viral infections; and second, we need the differentiation of naïve CD4+ T-cells into effector and memory subsets. At the same time, the infusion of a population of immune cells that has been in contact with COVID-19 and with immunological memory will create a quicker and more robust response. This way, we can give hope to patients suffering from COVID-19 with bad prognosis.

This clinical trial proposes the treatment of patients who have a worse prognosis due to SARS-CoV-2 infection, pneumonia and/or lymphopenia, by using a cell therapy approach.

This is an innovative and a non-pharmacologic intervention.

In this phase I/II trial, natural killer (NK) cells or memory T lymphocytes will be infused from donors who have recovered from COVID-19 and are disease free for at least 14 days.

The technical advantage is that these procedures are routinely performed at the Hematology and Hemotherapy Services of many hospitals. There is extensive experience in this type of selective separation of cell populations due to the remarkable hematopoietic stem cell transplantation activity. For this reason, the cell therapy strategies proposed in this study have shown to be essentially safe and can contribute to increasing the therapeutic options available in the current emergency situation due to the SARS-CoV-2 infection.

We expect a quick recovery of the patients with pneumonia or lymphopenia for two reasons:

1. NK cells are cells that act quickly after a viral infection. The number and function of NK cells correlated with the severity of another coronavirus infection (SARS) originated in China in 2002. Besides, we have previous successful experience with other virus such as CMV, EBV and HHV-6.

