## Screening Visit

## Subjects will be screened within two days before randomization and dosing to determine eligibility for participation in the study.

- Obtain written informed consent.

After the informed consent is signed, the following assessments will be performed:

- Review SARS-CoV-2 testing.
- Focused medical history including the following information: demographics, date of first symptom, description of symptoms, allergies, concomitant medications and past medical history.
- Targeted physical examination including vital signs (heart rate, temperature, blood pressure), body weight, and height.
- Documentation of respiratory status:
- Respiratory Rate
- SpO2 at rest or PaO2
- Fraction of inspired oxygen (FIO2)
- Oxygen supplementation:
  - nasal cannula
  - high flow oxygen therapy
  - mask with a reservoir bag
  - non-invasive ventilation
- Radiographic findings (chest X ray or chest CT).
- Obtain blood samples if not done in the previous 48 hours for:
- Hematology and coagulation: Hematocrit, Hemoglobin, Mean Corpuscular Hemoglobin Concentration (MCHC), MCV (Mean Corpuscular Volume), Platelets, Red blood cells, White blood cells with differential (Basophils, Eosinophils, Lymphocytes, Monocytes, Neutrophils). **D-Dimer.**

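### The fixed covariate list for the adjusted recovery ratio omits days since symptom onset, a baseline value the trial already records; adding it is a free improvement of low severity

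*Protocol*

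**What the plan says.** The Statistical analysis paragraph of the protocol (in the Study Population section) gives two analyses of Phase II recovery. The crude probabilities "will be compared by Chi-Square test". Separately, there is a covariate-adjusted "estimation of the ratio of probability of recovery in experimental treatment to standard of care", obtained by standardisation from a logistic model. Its covariates are fixed: "Covariates to be included will be age, sex, basal punctuation in WHO scale at baseline and presence of cardiovascular risk factors".

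Four other places bear on illness stage:

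- Inclusion criteria: "Onset of symptoms < 12 days prior to administration of study treatment".
- Screening Visit: the medical history includes "demographics, date of first symptom, description of symptoms".
- Primary outcome, Phase II: recovery is assessed "through Day 14". The study clock starts at Day 0, which the Baseline/Day 0 section defines as the infusion date.
- Subject Treatment Assignment: patients are first allocated to an arm by HLA typing, and "within each arm they will then be randomized in a 1:1 ratio to 1 of 2 treatment groups (SoC or SoC+RP2D"). No stratification by time since onset is mentioned.

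**The concern.** The outcome window is fixed in study days, but patients enter at different points of their illness. Someone who enters on the day of first symptoms is assessed up to illness day 14, and someone who enters 11 days later up to illness day 25. How long the illness has already run may well affect whether a patient has recovered by a fixed study day. None of the four listed covariates measures it directly: two patients with the same baseline WHO score can be at day 2 and day 11.

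The protocol gives illness timing some weight, since it restricts entry by it and collects the date. The choice of covariates is not left to a later document either, because the list is stated and closed.

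What is at stake is limited to the adjusted ratio. If the groups happen to differ in illness stage, the planned adjustment cannot take that into account, and adding the term after the data are seen would look post hoc. Some precision may also be lost.

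**Working it through.** **Group size.** The protocol's 82 comes from 45% v 64.29% recovery, one-sided alpha 0.05 and power 80%. The pooled two-proportion formula is n = [z(0.95)·√(2·p̄·(1−p̄)) + z(0.80)·√(p1(1−p1) + p2(1−p2))]² / (p2−p1)². With p1 = 0.45 and p2 = 0.6429 it gives 81.3, so 82 per comparison group. The figure reproduces. The protocol enrols 82 per HLA arm and splits each arm 1:1, so a comparison may in practice be 41 v 41. Both sizes are carried below.

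**Illness day at the end of the window.** Onset under 12 days means 0 to 11 whole days before Day 0.

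- Earliest: 0 + 14 = illness day 14.
- Latest: 11 + 14 = illness day 25.
- With the ±1 day visit window in the schedule of activities: 13 to 26.

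**Chance imbalance.** Assumption: onset is uniform on 0, 1, …, 11 days.

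- Variance = (12² − 1)/12 = 143/12 = 11.92, so SD = 3.45 days.
- SD of the difference in group means = 3.45·√(2/n): 0.76 day at n = 41 and 0.54 day at n = 82.
- 95% limits (×1.96): about 1.5 days and 1.1 days.

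A narrower spread shrinks this. If onset ran uniformly over 4 to 11 days (also an assumption), the SD would be 2.29 days and the imbalance SD 0.51 or 0.36 day.

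**Effect on the recovery ratio.** The documents give no association between onset and recovery, so the odds ratio (OR) per day is assumed. In each setting 3,000 trials were simulated, and the crude log risk ratio was compared with a logistic-standardised one that adjusts for onset only. The table gives the variance of the adjusted estimate divided by that of the crude one, with a true effect present.

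| OR per day | 41 v 41 | 82 v 82 |
| --- | --- | --- |
| 1.00 | 1.006 | 1.005 |
| 1.05 | 1.007 | 0.999 |
| 1.10 | 0.988 | 0.985 |
| 1.20 | 0.930 | 0.899 |

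The saving is therefore about nil up to 1.05, 1-2% at 1.10 and 7-10% at 1.20.

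**Validity without the covariate.** Over the same settings the average crude risk ratio was 1.43 to 1.45 against a true 1.43 (64.29/45). The one-sided type I error of the crude test was 0.040 to 0.051. Omission produces neither bias nor inflation.

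**Not computed.** The comparator is an unadjusted estimate. The gain from onset beyond age, sex, baseline WHO score and cardiovascular risk factors was not computed; it depends on how much illness-stage information those four already carry.

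**The case against.** The strongest reply is that nothing here is wrong. Four plausible covariates are pre-specified, randomisation balances onset in expectation, and another statistician might prefer a different prognostic variable. The benefit also rests on an association that the documents do not give. An odds ratio of 1.2 per day is already strong: over 11 days it compounds to 1.2¹¹ ≈ 7.4-fold odds, and 1.1 compounds to about 2.9-fold. Patients sick enough to be hospitalised with low saturation are unlikely to be spread evenly from day 0, so the uniform assumption probably overstates the imbalance. Most of this stands, and it is why the point is minor. What remains is that the variable is a recorded baseline value, known before treatment, and a closed list excludes it.

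Four stronger readings are tempting and are not supported:

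- *The primary comparison is unfair because patients at different illness stages are treated as alike.* Randomisation is within each arm, so the comparison and its type I error remain valid.
- *The omission affects an adjusted primary test.* The protocol tests recovery with a crude chi-square, and the covariates enter only the additional ratio estimate.
- *Adding onset raises the power of the trial.* In the simulation an onset-adjusted test rejected more often at an OR of 1.2 per day (0.58 v 0.55 at 41 per group, 0.83 v 0.81 at 82). The chi-square is unchanged by the fix, so this gain does not accrue to the protocol's test.
- *An imbalance at the 95% limit would distort the result.* For an assumed OR of 1.10 to 1.25 per day it would move the recovery difference by 3.4-7.2 points (41 v 41) or 2.4-5.1 points (82 v 82), against a planned 19.3. That is ordinary sampling variation, which the standard error already covers.

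Nor does the statement in the rationale that "NK cells are cells that act quickly after a viral infection" show that onset predicts recovery by Day 14. It describes NK-cell biology and does not concern the memory T-cell arm.

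**Conclusion.** The point holds as a free improvement of low severity. The closed covariate list leaves out a collected baseline value that varies by up to 11 days between patients whose recovery is counted over the same study days. The consequence is confined to the adjusted ratio: some precision forgone, and no protection against a chance difference in illness stage. Under uniform onset over 0-11 days that difference has an SD of 0.76 day (41 v 41) or 0.54 day (82 v 82).

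The variance saving runs from about nil to 10% for assumed odds ratios of 1.0 to 1.2 per day, measured against an unadjusted estimate. If onset does not predict recovery, nothing is lost by leaving it out. The validity of the trial's comparison is not in question.

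**What to change.** In the Statistical analysis paragraph, add days from first symptom to randomisation, as a continuous term, to the pre-specified covariates of the standardised recovery ratio. Do this before outcome data are seen.

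Count to randomisation rather than to infusion. The entry criterion is tied to administration of study treatment, and standard-of-care patients receive no infusion. Randomisation gives both groups one definition of the covariate.

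The cost is one line of text and one more model parameter. No new data are needed, and the chi-square test and the sample size stay as they are.
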